### Randomization and blinding

2.6

The randomized controlled trial (RCT) utilized a simple randomization method implemented via the PROC PLAN procedure in SAS 9.4 software, which was designed by an independent statistician. A fixed seed number of 60 was preset to ensure reproducibility, and participants were allocated to the two groups (30 each) at a 1:1 ratio, with random numbering from 01 to 60, generating 60 unique sequences to ensure unbiased group allocation. The group allocation information was sealed in tamper-evident opaque envelopes and managed by a blinded study coordinator who was not involved in participant recruitment or outcome assessment, ensuring strict allocation concealment.

During trial execution, consecutively enrolled participants meeting inclusion criteria were sequentially assigned unique identification numbers. The blinded trial coordinator strictly adhered to the enrollment chronology when unsealing pre-sequenced, tamper-evident sealed envelopes. The revealed allocation information was subsequently transferred to an independent investigator uninvolved in recruitment or intervention delivery, who executed group assignments per the predefined randomization matrix. The study protocol explicitly prohibited any deviation from allocation sequences or non-programmatic modifications.

The independent researcher, based on randomized allocation, preset the transcutaneous auricular vagus nerve stimulator (tVNS501) with fixed parameters (intensity: 20–40 mA, frequency: 80 Hz, pulse width: 100 μs, pulse 40–60s) and blinded the display screen using opaque tape before handing it to a clinical operator. In the active stimulation group, the device was powered to deliver real stimulation, while in the sham stimulation group, the device remained inactive (no current output) but maintained physical contact. A triple-blind design (participant-operator-outcome assessor) was implemented throughout the study to maintain blinding of group assignment (taVNS or sham taVNS). Unblinding was performed post-database lock by an independent statistician using SAS 9.4 (SAS Institute Inc., Cary, NC), strictly adhering to the predefined protocol. This study strictly adhered to the principle of observer independence in clinical research (Figure 1).

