**Methods/design:**

This double-blind randomized controlled trial will enroll 60 elderly patients (60–85 years) meeting ICSD-3 criteria for CI and Rome IV criteria for FD. Using block randomization with computer-generated sequences, eligible participants will be allocated 1:1 to either active taVNS group (*n* = 30) or sham control group (*n* = 30). The CFDA-certified transcutaneous vagus nerve stimulator (Model tVNS501, Reach Medical, China; Registration No. SuXieZhun20212090050) will be positioned at standardized anatomical sites: the concha cymba (the inferior margin of the intersection between the superior and inferior crura of the antihelix within the cymba conchae), electrical stimulation will deliver with fixed parameters (frequency: 80 Hz, pulse width: 100 μs, pulse 40–60s). The active group will receive validated taVNS parameters, while the sham group will undergo identical procedures without electrical output. Interventions will be administered 30 min per session, 5 sessions weekly for 3 consecutive weeks. Primary endpoints include changes in Pittsburgh Sleep Quality Index (PSQI) and Nepean Dyspepsia Symptom Index (NDSI) at week 3. Secondary outcomes encompass Insomnia Severity Index (ISI), 36-Item Short Form Survey (SF-36), and serum biomarkers (pro-inflammatory cytokines IL-1*β*, IL-4, IL-6, TNF-*α*, hs-CRP, TGF-β; neurotransmitters Dopamine (DA), serotonin (5-hydroxytryptamine, 5-HT), norepinephrine (NE), Glutamate (Glu), *γ*-aminobutyric acid (GABA)). Safety profiles will be systematically evaluated using CTCAE v5.0 criteria, with all adverse events documented throughout the study.

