#### Selection bias risks

2.11.1

To mitigate selection bias risks, this study implemented a rigorously designed RCT framework. Participants were stratified based on key baseline characteristics (e.g., age, disease severity) and subsequently allocated to intervention or control groups via computer-generated randomization sequences. This dual strategy of stratification and randomization ensured balanced distribution of confounding variables across study arms, thereby minimizing systematic differences between groups.

An independent statistician executed the randomization process to eliminate investigator interference in group assignment, while allocation concealment was maintained until participant enrollment to prevent selection bias arising from foreknowledge of treatment assignments. These measures collectively ensured inter-group comparability and mitigated potential biases associated with non-random allocation or investigator-driven participant selection.

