#### Design of the protocol

2.11.3

This study employed a prospective randomized double-blind RCT design, validated against international CONSORT guidelines. The randomization process is implemented through a computer-generated block randomization sequences. Participant allocation was executed by an independent statistician through an Interactive Web Response System (IWRS), ensuring allocation concealment until intervention initiation. A blind design (masking both investigators and participants) was implemented, with primary endpoints adjudicated by a blinded endpoint committee.

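### The protocol gives incompatible accounts of how participants were allocated, so its stratified-balance claim conflicts with its single list and no one can tell which analysis matches the design

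*Protocol article*

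**What the plan says.** The protocol article describes allocation in five places.

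- **Section 2.6 (Randomization and blinding).** The trial "utilized a simple randomization method implemented via the PROC PLAN procedure in SAS 9.4 software". There is one list, numbered 01 to 60, with 30 participants per arm. On concealment: "The blinded trial coordinator strictly adhered to the enrollment chronology when unsealing pre-sequenced, tamper-evident sealed envelopes". The revealed allocation then goes to an independent investigator, who makes the assignment.
- **Abstract, Methods/design.** "Using block randomization with computer-generated sequences, eligible participants will be allocated 1:1".
- **Section 2.11.1 (Selection bias risks).** "Participants were stratified based on key baseline characteristics (e.g., age, disease severity"), and were then randomised. The section says that this combination secured balance of confounders between the arms.
- **Section 2.11.3 (Design of the protocol).** "The randomization process is implemented through a computer-generated block randomization sequences", and "Participant allocation was executed by an independent statistician through an Interactive Web Response System (IWRS").
- **Section 2.11.5 (Blinding implementation).** Allocation is concealed from investigators by a central randomisation system.

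On analysis, section 2.8.5 plans t tests or one-way ANOVA for measurements and chi-square or Fisher tests for categories, with no stratum or baseline term. Section 2.11.2 adds multivariable regression on baseline covariates and gives age and gender as examples.

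**The concern.** These are positive statements about the same procedure, and they differ on the method (simple, blocked or stratified), on the mechanism (envelopes or a web or central system) and on who carried it out (an independent investigator or an independent statistician). This is not detail that an article may leave to the full protocol, such as a block size. No further document could make all the statements true together.

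Two things are at stake. First, a property the trial relies on, balance secured by stratification, is claimed in one section and ruled out by the procedure in another. Second, the primary analysis should reflect the way participants were allocated, and a reader cannot tell which way that was. The method, the concealment mechanism and the person implementing them are also what a reader needs in order to judge the risk of bias from allocation.

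**Working it through.** No computed figure in the plan is in dispute here. The check sets the accounts side by side.

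**1. Can the section 2.6 list be simple randomisation?** Inputs from section 2.6: 60 numbers, 30 per arm (30 + 30 = 60). Under simple 1:1 randomisation each participant has probability 1/2 of active treatment, whatever came before. On a list constrained to 30 per arm, after k allocations of which a are active, the next is active with probability (30 − a)/(60 − k). This depends on the past. It is 0 once a = 30, and the 60th allocation is fully determined by the first 59. PROC PLAN can produce such a list as a random permutation, so the 30/30 split is perfectly possible. The label simple is what is wrong: this is restricted randomisation, in effect one block of 60.

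**2. Can that list be stratified?** Stratified allocation needs a separate sequence for each stratum, or an algorithm that reads the participant's stratum. Section 2.6 has one sequence, and the next envelope is set by order of enrolment alone. Age and severity play no part. So if section 2.6 is true, the stratification in section 2.11.1 did not happen, and the arms are balanced on these factors only in expectation. With 30 per arm, chance imbalance in baseline severity remains possible.

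**3. Can both mechanisms be true?** In section 2.6 a coordinator opens a physical envelope and an independent investigator assigns. In section 2.11.3 an independent statistician allocates through a web system. No section says that one served as backup for the other.

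**4. Is the coordinator blinded?** The coordinator opens the envelope and the allocation is thereby revealed. Unless the contents are coded, which the text does not say, that person knows the arm.

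**5. Which analysis fits?**

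| If allocation was | Tests in section 2.8.5 | Regression in section 2.11.2 |
|---|---|---|
| One list, 30 per arm | Fit | Optional; baseline score not named |
| Blocked, no strata | Commonly accepted | Optional; baseline score not named |
| Stratified by age and severity | Ignore the strata | Age named, severity not named |

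In the last row, let R² be the share of outcome variance explained by the strata. With allocation balanced within strata, the true standard error of the arm difference is about √(1 − R²) times the one the unadjusted t test reports. The reported error is therefore too large by a factor of about 1/√(1 − R²). The document gives no R² for age or severity, so the direction is known but the size is not.

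**The case against.** The strongest reply is that section 2.6 is the real account and the rest is loose wording. Section 2.11.5 names a stroke scale (NIHSS) as an example of the scales used for the primary endpoints, although it is not an outcome here, which suggests that section 2.11 holds text not written for this trial. A list fixed at 30 per arm can also be called a single block, which softens the clash between simple and block. Both remarks have force. But the abstract also says block, nothing marks section 2.6 as the governing text, and neither remark rescues the stratification claim or the second mechanism.

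Four stronger readings are tempting, and the document does not support them.

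- **The analysis cannot match the design.** Unadjusted tests suit an unstratified list and are commonly accepted after blocking. Only the stratified account gives a mismatch, and section 2.11.2 already names age. Its list is illustrative, so severity might be included. Where a mismatch exists, standard errors that are too large are conservative and do not create false positives.
- **A 30/30 split is improbable.** Independent coin-tossing would give exactly 30/30 with probability C(60,30)/2^60 = 0.103, but section 2.6 describes a fixed list, not coin-tossing. Arm sizes also say nothing about covariate balance, and unequal arms would cost almost no power: 0.987 at 30/30 and 0.985 at 24/36 (two-sided pooled test, 20% against 70%).
- **Concealment failed.** Opaque sealed envelopes and a web system can each conceal allocation. What is undetermined is which one was used.
- **The list can be rebuilt because the seed is printed.** Section 2.6 does say "A fixed seed number of 60 was preset to ensure reproducibility". However, the code, the factor order and the mapping to arms are not given, and the document does not say whether any envelopes were still unused. Redrawing the list would also conflict with section 2.6, which forbids departures from the sequence.

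On the coordinator, section 2.6 places this person outside recruitment and outcome assessment and defines the blind as covering participant, operator and assessor. The mislabel therefore shows no route to bias. It is still a wrong description.

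**Conclusion.** The point holds as a contradiction on a property the trial relies on, with a direct link to the primary analysis. At least some of the statements in section 2.6, the abstract and sections 2.11.1, 2.11.3 and 2.11.5 are wrong. Under section 2.6 the stratified-balance claim is false and the label simple is incorrect. The coordinator's description is wrong unless the envelopes held only codes.

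The supportable conclusion on analysis is that nobody can tell which one matches, because the design is not fixed in the text. The sample size is unaffected, and any effect on the result is confined to the precision of the primary comparisons: standard errors somewhat too large if strata were used and ignored, or avoidable exposure to chance baseline imbalance if they were not. This rests on reading each section as a statement about this trial. If the sponsor confirms that section 2.6 alone is accurate, what remains is corrected wording and a baseline-adjusted primary model.

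**What to change.** 1. State the one allocation method and the one concealment mechanism actually used since first enrolment on 26 July 2024 (section 2.1), naming the role that carried it out. Delete the other accounts from the abstract and from sections 2.6, 2.11.1, 2.11.3 and 2.11.5 as needed.
2. If the single list was used, call it restricted randomisation with 30 per arm and remove the claim that stratification secured balance. Adjust the primary PSQI and NDSI comparisons at week 3 for the baseline value of the same score and for age.
3. If allocation was stratified, name the strata and put them in the primary PSQI and NDSI models.
4. Say in section 2.8.5 that this adjusted model is the primary one, so that it does not compete with the unadjusted t test or with section 2.11.2.
5. Describe the coordinator as unblinded and, if this is so, outside recruitment, treatment and assessment.

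The cost is wording and one or two model terms. Age and baseline PSQI and NDSI are already collected (sections 2.8.1 and 2.8.2), so no new data, participants or procedures are needed. The change should be made before unblinding.

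### Section 2.6 prints the randomisation seed with most of the recipe for the list, an avoidable threat to concealment and blinding if that recipe was the one used

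*Protocol article*

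**What the plan says.** Section 2.6 (Randomization and blinding) says the list was "implemented via the PROC PLAN procedure in SAS 9.4 software". It then says "A fixed seed number of 60 was preset to ensure reproducibility", that "participants were allocated to the two groups (30 each) at a 1:1 ratio", and describes the list as made "with random numbering from 01 to 60, generating 60 unique sequences".

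The link from list to patient is also given. Eligible participants are "sequentially assigned unique identification numbers", and the coordinator "strictly adhered to the enrollment chronology when unsealing pre-sequenced, tamper-evident sealed envelopes". List position is therefore enrolment order.

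The protections named in Section 2.6 are opaque tamper-evident envelopes, a coordinator outside recruitment and assessment, an independent person who sets the device, and tape over its display. On that basis the section claims strict concealment, says "A triple-blind design (participant-operator-outcome assessor) was implemented throughout the study", and places unblinding after database lock.

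Other parts describe the randomisation differently. The Abstract says block randomisation. Section 2.11.1 says participants were stratified, with age and disease severity as examples. Section 2.11.3 says block sequences delivered through an interactive web system, "ensuring allocation concealment until intervention initiation".

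**The concern.** A seeded generator returns the same list each time it is run with the same program; that is the purpose of fixing a seed. Whoever holds the seed and can work out the program can produce the list without touching an envelope. The named safeguards protect the paper list and the device display. None of them bears on recomputing the list, and nothing in the article says the seed was withheld from recruiters, operators or assessors.

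Two protections would be exposed. A recruiter with a rebuilt list would know the next assignment before deciding whom to enrol. An operator or assessor would know the arm of participants already enrolled. Both primary endpoints, PSQI and NDSI, are symptom scales, on which expectation and the manner of assessment can shift the difference between arms. Selection or assessment bias of this kind cannot be reliably removed in the analysis.

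**Working it through.** The document gives no figure to reproduce here. The check is which inputs of the list are disclosed and how much uncertainty they leave.

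**Disclosed in Section 2.6:** seed 60 (equal to the total sample size), PROC PLAN, SAS 9.4, numbers 01 to 60, 1:1 with 30 per arm, envelopes used in enrolment order.

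**Not disclosed:** the exact PROC PLAN statements, how the output maps to envelopes, and which code is which arm.

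**Uncertainty without the seed.** The number of 60-patient lists with 30 per arm is C(60,30) = 118,264,581,564,861,424, about 1.18 × 10^17, or log2 = 56.7 bits.

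**Uncertainty with the seed.** Only program layout and arm coding remain open. Let K be the number of plausible layouts. The document gives no value, so K = 10 to 100 is assumed. A wrong list agrees with m known codes by chance with probability of about 1/2^m, so the expected number of wrong lists still fitting is K/2^m:

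| Known codes m | K = 10 | K = 50 | K = 100 |
|---|---|---|---|
| 5 | 0.31 | 1.56 | 3.13 |
| 8 | 0.04 | 0.20 | 0.39 |
| 10 | 0.01 | 0.05 | 0.10 |

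The 30/30 constraint changes little. For ten known codes split 5/5, the chance of agreement is C(50,25)/C(60,30) = 0.00107, about 1/936, against 1/2^10 = 1/1024.

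**Where known codes could come from.** Section 2.8.4 has a group code (A or B) written on every blood tube and cap, so anyone who handles tubes has codes to check a candidate list against, up to a swap of the two labels. Section 2.6 says the sham delivers no current, so absence of sensation could suggest which label is active.

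**Dependence on the true method.** These figures apply only if Section 2.6 is the method used. With blocks of unstated size, strata, or a web system with its own list, the printed recipe need not reproduce the allocations. Under stratification, list position need not equal enrolment order. Even the description of Section 2.6 as simple randomisation is loose: independent 1:1 draws give exactly 30/30 with probability C(60,30)/2^60 = 0.103, so a guaranteed 30 per arm implies a constrained list.

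SAS was not available, so no list was rebuilt.

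**The case against.** The strongest reply is that exposure is assumed. Fixing a seed is good practice, and publishing it after database lock is good reporting. The article condenses a protocol that is not shown, and it does not say that recruiters, operators or assessors were given the seed. Enrolment began on July 26, 2024 (Section 2.1), but no end date is given. Section 2.6 is in the past tense, including the unblinding, while the Abstract is in the future tense. If enrolment had closed before the seed became readable, concealment could not have been harmed. If the database was also locked, there is no fault in printing it. This stands, and it makes the point conditional.

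Three further replies stand in part:

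- The recipe works only if Section 2.6 is the true and complete method, which three other places put in doubt. This limits the claim; it does not make early disclosure of a seed safe.
- The number of layouts is an assumption, and the calculation needs codes that are known without error. With mistaken guesses even the true list would fail to match all of them, so more would be needed.
- If staff can tell the arm from sensation, the zero-output sham has already weakened the blind. For those participants the seed adds little, but it would add the arms of participants not observed and of those not yet enrolled.

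A reader might infer that concealment and blinding have failed, or that all 60 allocations can be read off. The document does not support either: using the seed would take deliberate effort, the code and arm coding are missing, and no use of it is recorded.

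**Conclusion.** The point holds as an avoidable, conditional threat to concealment and blinding. Section 2.6 discloses the seed with the procedure, version, length, ratio and order of use, while claiming that allocation stays hidden until lock. If that section describes the real method, the printed inputs reduce about 1.18 × 10^17 possible lists to a small set of program variants. Under the assumed 10 to 100 variants, ten correct codes would be expected to leave at most about 0.10 wrong ones.

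The conclusion rests on three things that the article leaves open: that the list was made as Section 2.6 says, that someone with a role in recruitment, delivery or assessment could read the seed before lock, and that the missing code can be guessed. It is not a finding that anyone did so. The envelopes, tape and separation of roles remain useful against ordinary disclosure, but they do not protect against recomputation.

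**What to change.** 1. Keep the seed and program in a restricted file held by the independent statistician until database lock, and report them only afterwards. Deleting the seed from a text that staff may already have read conceals nothing by itself.
2. If any numbers are still unallocated, have the independent statistician generate the remaining list, preserving 30 per arm, with an undisclosed seed unrelated to any trial figure. Section 2.6 forbids departures from the sequence, so this needs a documented amendment. It protects future allocations only; it does not restore the blind for participants already assigned.
3. Reconcile Section 2.6 with the Abstract and Sections 2.11.1 and 2.11.3: simple, block or stratified, and envelopes or web system.
4. In the final report, state who had access to the seed, from what date, and how many participants were enrolled or assessed after that date.

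The cost is an amendment, a new set of envelopes for unused numbers, and later publication of the seed. If enrolment is complete, step 2 falls away. If the database is already locked, only steps 3 and 4 remain.

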**Figure 1 fig1:**
[figure not shown]
TaVNS Stimulation Device and Example Diagram of Electrode Placement.

### Intervention

2.7

Following standardized screening, all participating clinicians underwent unified training in both taVNS and sham taVNS protocols. The informed consent form explicitly stated that the study involved two distinct neuromodulation interventions (which may differ in electrical sensation and therapeutic responses). Training modules included: (1) Device operation: standardized procedures for power cycling and locked parameter interfaces; (2) Anatomical localization: precise electrode placement at the tragus: the inferior margin of the intersection between the superior and inferior crura of the antihelix within the cymba conchae and the junction of the inferior crus of the antihelix and the auricle within the cymba conchae using auricular anatomical charts; (3) Blinding maintenance: standardized communication protocols to prevent unintentional disclosure of group allocation. All interventions were conducted in standardized treatment rooms within the hospital inpatient department.

All clinicians participating in this study were required to have at least 2 years of standardized acupuncture practice. Participants were placed in a supine position, and the auricular stimulation areas were cleaned with 75% ethanol solution followed by placement of ear clips. The clinically trained operator, blinded to group assignment, using transcutaneous auricular vagus nerve stimulators (tVNS501), precisely placed bipolar electrodes at standardized anatomical sites: the concha cymba (the inferior margin of the intersection between the superior and inferior crura of the antihelix within the cymba conchae). The intervention protocol consisted of 30-min sessions, administered weekdays from 9:00 to 11:00 AM for three consecutive weeks (15 sessions total).

Participants shall be withdrawn from the trial and provided with appropriate medical interventions under any of the following circumstances: (1) occurrence of serious adverse events; (2) voluntary withdrawal request from the participant; (3) clinical deterioration of the underlying condition; (4) requirement for prioritized treatment of other medical disorders; or (5) development of localized irritation or allergic reactions.

